### Outcomes

The primary outcome of the current study is safety based on the overall 90-day postoperative morbidity rate, analysed and classified according to Clavien–Dindo [20]. Secondary outcomes include (1) intraoperative complications (i.e. vascular injury, injury to other organs), (2) 90-day mortality, (3) conversion rate, (4) operative time (minutes), (5) blood loss (millilitres), (6) validated assessment of the whole procedure using a CAT, (7) grading of the resection specimen according to Benz et al. [21], (8) total lymph node count in the specimen by the pathologist, (9) number of resected tumour-positive lymph nodes, (10) resection margins, (11) completeness of mesocolic excision based on the postoperative CT imaging (as performed 1 year postoperatively in regular oncological follow-up), (12) frequency of locoregional recurrence, (13) occurrence of distant metastasis, (14) 3-year DFS, (15) 5-year OS and (16) long-term surgical morbidity such as incisional hernia and adhesion-related small bowel obstruction.

### Sample size calculation

The sample size calculation is based on safety with non-inferiority for the primary endpoint, the overall 90-day morbidity. In the Dutch national colon cancer audit, the overall postoperative complication rate after MIRH was 26% [22]. As all contributing hospitals within this study are represented in the national database, it can be assumed that the control cohort of the Right study has the same percentage of postoperative complications, i.e. 26%. A non-inferiority margin of 7% was defined. Therefore, introducing the new standardised technique will still be considered safe if the overall postoperative complication rate does not exceed 33%. A total of 1095 patients (365 patient in each of the three prospective cohorts) will be needed to show that there is no difference between the control and experimental (i.e. standardised surgical technique) treatment. With this number of included patients, it can be demonstrated with 80% certainty that the lower limit of the one-sided 95% confidence interval (or equivalently a 90% two-sided confidence interval) will be above the non-inferiority limit of 7%.

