**Fig. 1 Fig1:**
[figure not shown]
Schematic of the five-step approach of the Right study

*Phase 1*: the variation of current surgical techniques amongst surgeons and centres for right-sided colon cancer was evaluated by prospective inclusion of consecutive patients into the *control cohort*. The first patient was included in October 2021, and currently all patients for this phase of the study have already been included. The preoperative CT imaging, full-length surgical video, pictures of the front and the back of the specimen and clinicopathological outcomes, as well as the CT imaging 1 year postoperatively (which is part of the routine oncological follow-up regimen in the Netherlands) were collected. The patients were treated according to the surgeon’s preference of surgical technique and local hospital perioperative care protocols. In this phase, anonymised video analysis of all the cases will be performed to evaluate variability and surgical quality.

*Phase 2*: a Delphi method was applied with two colorectal surgeons from each participating institution (*n* = 43) after the inclusion period of the control cohort was closed, to establish a detailed standardised technique of MIRH for colon cancer. The consented standardised technique includes essential elements that could potentially improve outcomes such as setup, surgical approach, mesocolic plane dissection, level of vascular ligation with the extent of vertical lymphadenectomy, the technique of the anastomosis and the extraction site.

*Phase 3*: the consented standardised technique was taught to all participating colorectal surgeons (*n* = 86) during a 1-day hands-on surgical *training* course. The standardised MIRH was trained in several skills centres in the Netherlands. The same two surgeons from each participating centre who contributed in the second phase participated in this phase. The courses consisted of a theory session with several presentations about the best evidence, anatomy and the optimal standardised surgical technique, followed by a hands-on training on human cadavers in the afternoon to apply and practise the technique. All proctors of the Right study first participated in a teach the teacher MIRH CME training in the presence of ESCP faculty before training the participating surgeons.

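### The sample size section gives two safety criteria that are not equivalent (a fixed 33% ceiling and a confidence limit against 7 points, printed in the wrong direction) and does not say which decides

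*Protocol article*

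**What the plan says.** All of the following is in the protocol article. The section Sample size calculation takes its planning rate from an external source: "In the Dutch national colon cancer audit, the overall postoperative complication rate after MIRH was 26" per cent. It carries that rate over to the study: "it can be assumed that the control cohort of the Right study has the same percentage of postoperative complications, i.e. 26" per cent. It then sets the margin, "A non-inferiority margin of 7% was defined", and concludes that "introducing the new standardised technique will still be considered safe if the overall postoperative complication rate does not exceed 33" per cent. This is the only sentence in the article that says what result counts as safe.

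Two sentences later, the section ties the sample size to a comparison of control and experimental treatment. It refers to a "one-sided 95% confidence interval (or equivalently a 90% two-sided confidence interval") and asks for the lower limit to lie above the 7% limit.

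Other sections are comparative. Study design sets the intervention cohorts against the study's own control cohort, Study objectives aims not to increase the complication rate, and Phase 5 in Study outline collects data for comparison with the control cohort. On the state of that cohort, Phase 1 says that "currently all patients for this phase of the study have already been included".

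**The concern.** One criterion is an absolute ceiling on the rate with the new technique. It names neither the observed control rate nor a confidence limit. The other concerns a confidence limit and the margin. They share a boundary only if the control rate is 26%. Even then they differ, because one ignores sampling error and the other does not.

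The second criterion cannot be applied as printed. For intervention minus control, a lower limit above +7 points would show that the new technique is worse by more than the margin. The intended condition is an upper limit below +7 or, with the difference taken as control minus intervention, a lower limit above −7. A reader who needs a workable rule is therefore left with the 33% sentence.

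Patient safety is the primary outcome, so the choice between the two rules could change the study's main conclusion.

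**Working it through.** **Inputs.** From Sample size calculation: control rate 26% (assumed there), margin 7 points, one-sided 5%, power 80%, 365 per cohort and 1095 in total. No dropout is stated, so none is applied. Assumptions made here: the implementation and consolidation cohorts are pooled to 730 (the article does not say so), and the control rates other than 26% are examples.

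**Step 1: reproduce the plan's figure.** For a two-sample non-inferiority comparison with equal true rates p and r intervention patients per control patient:

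n(control) = p(1−p)(1 + 1/r)(z₀.₉₅ + z₀.₈₀)² / margin²

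- r = 2: 0.1924 × 1.5 × (1.645 + 0.842)² / 0.0049 ≈ 364.1, rounded up to 365. With 730 intervention patients the total is 1095, an exact match (power 80.1%).
- r = 1: 486 per cohort, no match. With 365 against 365 the power is 69.5%.
- One-sample test against a fixed 33%: 0.1924 × (1.645 + 0.842)² / 0.0049 ≈ 242.8, so 243 patients, no match.

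The sample size was therefore built on a comparison with the control cohort, not on the ceiling.

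**Step 2: the two rules.**

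- Ceiling: observed rate at most 33%, that is at most 240 of 730 (0.33 × 730 = 240.9) or 120 of 365 (0.33 × 365 = 120.45). The pass probability is exact binomial.
- Difference rule: upper one-sided 95% limit of intervention minus control below 7 points, 365 against 730. The pass probability is Φ[(0.07 − d)/SE − 1.645], where d is the true difference and SE = √[p₁(1−p₁)/365 + p₂(1−p₂)/730].

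**Step 3: pass probabilities, 730 intervention patients.**

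| True control | True new | Difference | Ceiling passes | Difference rule passes |
|---|---|---|---|---|
| 26% | 33% | 7 points | 49% | 5% |
| 20% (assumed) | 30% | 10 points | 96% | 0.3% |
| 35% (assumed) | 35% | 0 | 12% | 74% |

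Worked example for the second row: SE = √(0.16/365 + 0.21/730) = 0.0269; (0.07 − 0.10)/0.0269 − 1.645 = −2.76; Φ = 0.003.

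The first row does not depend on pooling: with one cohort of 365, a true 33% passes the ceiling about 50% of the time.

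**Step 4: the same gap on the observed scale.** If the control cohort shows 26%, the difference rule passes an observed intervention rate up to 28.2% (206 of 730), not 33%. At 240 of 730 (32.9%) the difference is 6.9 points and the upper limit is 6.9 + 1.645 × 100 × √(0.1924/365 + 0.2207/730) ≈ 11.6 points.

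**Step 5: drift from the margin.** The excess that the ceiling allows is 33 minus the control rate: 13 points at 20%, 7 at 26%, −2 at 35%. A confidence limit around the 33% would not cure this. With a one-sample upper 95% limit required to lie below 33%, 20% against 30% still passes with probability Φ[0.03/√(0.21/730) − 1.645] = 0.55.

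**The case against.** The strongest reply is that 33% was never meant as the decision rule. The sentence stands in a sample size section and follows as a consequence from an explicitly assumed control rate and a stated margin. Giving the largest tolerable true rate under the planning assumption is ordinary non-inferiority wording. The sentence does not say that an observed point estimate will be held against 33%. The design and objectives are comparative, and the sample size reproduces only as a two-sample comparison.

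Much of this stands. A reader might infer that the plan ignores its control cohort, or that the study will reach wrong verdicts. The documents support neither. A reader might also infer that the 26% is wrong, because the eligibility criteria exclude higher-risk patients and no follow-up window is given for the audit figure. The article shows no direction for such a difference and no observed control rate. Complete enrolment of the control cohort does not mean that its 90-day outcomes are final.

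What the reply does not remove is the conflict. The text does not label 33% as an illustration, and the competing sentence is reversed. The Statistical analysis section does not settle the matter: for dichotomous outcomes it names chi-square and regression methods and a 0.05 significance level, and the decisions it reserves for the later analysis plan concern stratification, subgroups and baseline imbalance. The point is therefore about what is stated, not about detail left to that plan.

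**Conclusion.** The point holds as an unresolved conflict between two stated safety criteria, one of them printed in the wrong direction. It does not hold as a claim that the plan disregards its controls. If the ceiling were applied to the observed rate, the chance of calling a true 33% safe would be about 49% rather than 5%, even with the planning assumption exactly right. That result rests only on reading the sentence literally and barely changes without pooling. The other scenarios (96% against 0.3%, and 12% against 74%) rest on assumed control rates of 20% and 35% and on pooling; they show how the rules diverge and are not forecasts. The wording should be settled before the cohorts are compared.

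**What to change.** In Sample size calculation, either delete the 33% or label it as an illustration of the margin at a 26% control rate. Replace the confidence-limit sentence with one criterion: non-inferiority is shown if the upper limit of the two-sided 90% confidence interval for the intervention rate minus the observed control-cohort rate is below 7 percentage points. Carry the same sentence into the statistical analysis plan.

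The cost is wording only; sample size and data collection do not change. Once the observed control rate is available, the power could be restated at that rate (for 365 against 730 with equal rates: 86% at 20%, 80% at 26%, 74% at 35%). This is optional and corrects no error.

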## Abstract

**Purpose:**

Minimally invasive right hemicolectomy (MIRH) is the cornerstone of treatment for patients with right-sided colon cancer. This operation has evolved during recent decades, with many innovations and improvements but this has also resulted in high variability of uptake with subsequent substantial variableness. The aim of this ongoing study is to identify current surgical variations, determine the most optimal and standardised MIRH and nationally train and implement that technique to improve short-term clinical and long-term oncological outcomes.

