Substantial procedural variation in MIRH for right-sided colon cancer is present [4–6]. Minimal invasive surgery has been widely adapted, but the technique has been evolving during almost 30 years [7]. In the last decade, there has been specific focus on low-pressure pneumoperitoneum, intracorporeal anastomosis, extraction site and complete mesocolic excision (CME) technique. CME encompasses a dissection along the embryological planes to create an intact envelope of mesocolic fascia with a central vascular ligation to include all the draining lymph nodes along the supplying segmental vessels [8–12]. There is a disparity between current medical practice and the recommendations from best evidence and international guidelines regarding several steps of the MIRH, and there were also considerable regional differences [6]. These resemble the reality in surgical practice due to an absence of regular training programs, and a lack or a delay of implementation is present for the majority of innovations. Standardisation and subsequent training of surgical techniques and credentialing of surgeons have been found to reduce the adjusted in-hospital mortality [13, 14]. Recently, a large cohort study demonstrated that high surgical quality is associated with a better long-term survival of patients with colorectal cancer [15].

The current ongoing study aims to educate, train and implement a standardised minimally invasive surgical technique for right-sided colon cancer according to the latest and best evidence. The primary objective is to implement the new technique safely without an increase in the 90-day postoperative complication rate, while improving long-term oncological outcomes. The secondary objective is to validate a procedure-specific competency assessment tool (CAT) for this operation and use it to assess surgical quality to demonstrate the added value of training and proctoring and to correlate surgical quality with patient-related outcomes.

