### Study objectives

The primary objective of this study is to safely implement a standardised technique of MIRH without increasing the 90-day postoperative complication rate, and to ultimately improve long-term outcomes for patients with right-sided colon cancer in the Netherlands. It is hypothesized that this will translate into a reduction of local and distant disease recurrence and thereby an improved 5-year overall survival (OS) and 3-year disease-free survival (DFS).

Secondary objectives are (1) to evaluate current national surgical variations of MIRH and their impact to clinical outcomes (already finished, namely phase 1); (2) to reach consensus concerning the standardised stepwise surgical technique for MIRH using the most recent insights from literature and guidelines and using the Delphi method (already finished) [18]; (3) to design and validate a CAT for the MIRH reflecting all the steps from the Delphi consensus; (4) to evaluate the effect of training and proctoring of the standardised MIRH (comparing control, implementation and consolidation cohorts) on surgical quality and (5) on short- and long-term clinical outcomes.

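### The sized test can only exclude a 7-point rise in 90-day complications, yet the text says it will show no difference and words the objective as no increase

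*Protocol article*

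**What the plan says.** The primary objective appears twice in the protocol article, both times without a margin. The Background section aims to "implement the new technique safely without an increase in the 90-day postoperative complication rate", and the Study objectives section aims to "safely implement a standardised technique of MIRH without increasing the 90-day postoperative complication rate".

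The Sample size calculation section then sets the test: "The sample size calculation is based on safety with non-inferiority for the primary endpoint, the overall 90-day morbidity". It takes 26% as the control rate from the national audit, states that "A non-inferiority margin of 7% was defined", and accepts the new technique as safe up to a rate of 33%. It goes on to say that 1095 patients "will be needed to show that there is no difference between the control and experimental" treatment, and closes by giving 80% power with a one-sided 95% (two-sided 90%) confidence interval.

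The Statistical analysis section names the chi-square test, with p below 0.05, for dichotomous data. It says that the analysis plan will be completed before the data are locked.

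**The concern.** Three different conclusions are attached to one test: no difference, no increase, and an increase smaller than 7 points. Only the third is what a one-sided non-inferiority test with this margin can establish. A claim of no difference would at least need a two-sided equivalence test with its own limits. A literal claim of no increase would need a margin of zero.

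What is at stake is the wording of the primary conclusion. The Discussion explains that safety was made the primary outcome because added operative risk could cancel any oncological gain. If the test is passed, the conclusion should therefore say how large an increase has been ruled out. The phrase about no difference also sits badly beside the chi-square test, because together they invite a reader to take a non-significant result as evidence of safety.

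**Working it through.** **Inputs, all from the Sample size calculation section.** Control rate 26% ("the overall postoperative complication rate after MIRH was 26" per cent); margin 7 percentage points; one-sided alpha 5%; power 80%; 365 patients in each of three cohorts. Equal true rates of 26% are my reading of the calculation. The contrast is not named.

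**Reproducing the sample size.** With k intervention patients per control patient, the control group needs

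n = (1.645 + 0.842)² × 0.26 × 0.74 × (1 + 1/k) / 0.07².

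- k = 1: n = 486 per group, which does not match.
- k = 2: n = 364.1, rounded up to 365 control and 730 intervention, 1095 in total. This matches exactly.

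Power check for 365 against 730: SE = √(0.1924/365 + 0.1924/730) = 0.0281, and Φ(0.07/0.0281 − 1.645) = 80.1%. So the stated number is a non-inferiority number, and it is consistent with the control cohort against the two later cohorts pooled. One later cohort against control (365 against 365) has 69.5% power.

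**What passing the test allows.** The criterion is that the upper limit of the two-sided 90% interval for (standardised minus control) lies below +7 points. Take 95/365 = 26.0% in the control cohort.

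- Pooled, 207/730 = 28.4%: difference +2.3 points; SE = √(0.2603 × 0.7397/365 + 0.2836 × 0.7164/730) = 0.0284; 90% interval 2.33 ± 1.645 × 2.84, that is −2.3 to +7.0 (upper limit 6.998). This passes, and one more event fails.
- One cohort, 100/365 = 27.4%: difference +1.4 points, 90% interval −4.0 to +6.8. This passes, and one more event fails.

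In both cases the observed rate is higher than in control and the test succeeds. Neither interval shows that a rise has occurred, since both include zero. Neither shows that no rise has occurred.

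**True rises below the margin.** P(pass) = Φ((0.07 − d)/SE − 1.645), with SE recalculated at each rate:

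| True rise d | 365 vs 730 | 365 vs 365 |
|---|---|---|
| 0 | 80% | 69.5% |
| 1 point | 68% | 58% |
| 2 points | 55% | 45% |
| 3 points | 41% | 33% |
| 7 points | 5% | 5% |

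**Why the other two conclusions are out of reach.** With a margin of zero and equal rates, the formula gives Φ(−1.645) = 5% at any sample size, so no number of patients shows literally no increase when the rates are equal. For two-sided equivalence within ±7 points, 365 against 730 has power of about 2 × 0.801 − 1 = 60%, and 80% power would need about 505 + 1010 = 1515 patients.

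**The chi-square route.** An illustration: 95/365 (26.0%) against 226/730 (31.0%). The pooled proportion is 321/1095 = 0.293, z = 0.0493/0.0292 = 1.69 and p = 0.09, so the difference is not significant. The upper limit of the 90% interval is 4.93 + 1.645 × 2.86 = +9.6 points, so non-inferiority fails. A non-significant test cannot stand in for the non-inferiority test.

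**The case against.** The strongest reply is that the qualification is already on the page. The Sample size calculation section opens with non-inferiority, states the margin and the 33% ceiling, and returns to the non-inferiority limit right after the loose phrase. Both statements of the objective speak of safe implementation, and this section defines safe by the margin. That stands, and it is why the point is minor. It does not make the phrase about no difference correct, and it does not put the margin into the two statements of the objective.

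It is also fair that the pass probabilities above belong to any non-inferiority test. They would be the same after rewording. They show what success does not rule out and do not measure a fault in the design.

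A reader might infer more than the documents support:

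- *That a real rise will be reported as no increase.* The article fixes no concluding sentence or reporting rule, so this is a risk created by the wording and not a planned step.
- *That an improvement could not be tested.* The chi-square test is named for dichotomous outcomes and could detect a reduction.
- *That the Abstract adds a further, conflicting claim.* Its aim to "nationally train and implement that technique to improve short-term clinical and long-term oncological outcomes" does not mention 90-day complications. Short-term clinical outcomes also appear among the secondary objectives.
- *That safety is a formal gate.* The Discussion expresses an expectation if the safety goal is met, and makes no phase or decision conditional on the test.

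**Conclusion.** The point holds as an error in the stated conclusion. Success excludes a rise of 7 points or more and shows neither no difference nor no increase. The sample size reproduces, and nothing here challenges the alpha or the margin. Whether 7 points is clinically acceptable cannot be judged from this document.

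The size of the gap can be put this way: with about 26% observed in control, an observed rise of up to 2.3 points (pooled contrast) or 1.4 points (one cohort) still passes. These figures assume unpooled normal-approximation intervals. The pooled contrast is inferred from the arithmetic and is not stated. A true rise at the margin passes about 5% of the time, as designed. Severity is minor.

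**What to change.** 1. In the Sample size calculation section, replace the phrase about no difference with: *to show, assuming equal true rates of 26%, that any increase in the 90-day complication rate is less than 7 percentage points*.
2. In the Background and Study objectives sections, tie the objective to the margin: *without an increase of 7 percentage points or more*. Leave the implementation and long-term aims as they are.
3. State that the primary conclusion rests on the upper limit of the two-sided 90% confidence interval for (standardised minus control) lying below +7 points, reported with the estimate and the interval. This also settles the direction: the section now speaks of a lower limit above 7%, which does not fit a difference in complications taken this way round.
4. State that neither a non-inferiority result nor a non-significant chi-square test may be reported as no increase or no difference.
5. Optional: once non-inferiority is met, a reduction may be claimed on the same prespecified contrast if the two-sided 95% interval lies wholly below 0. This fixed order costs no alpha.

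The cost is wording in the protocol and analysis plan, with no extra patients. The downside is a less favourable permitted claim.

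### The non-inferiority rule names the wrong confidence limit or the wrong sign, contradicting the 33% ceiling in the same section

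*Protocol article*

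**What the plan says.** All the relevant statements are in the Sample size calculation section of the protocol article.

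- Basis: "The sample size calculation is based on safety with non-inferiority for the primary endpoint, the overall 90-day morbidity".
- Control rate: from the national audit, it is assumed that "the control cohort of the Right study has the same percentage of postoperative complications, i.e. 26" per cent.
- Margin: "A non-inferiority margin of 7% was defined".
- Meaning of the margin: the new technique "will still be considered safe if the overall postoperative complication rate does not exceed 33" per cent.
- Planning assumption: 1095 patients, 365 in each of three cohorts, "will be needed to show that there is no difference between the control and experimental (i.e. standardised surgical technique) treatment".
- Power: "it can be demonstrated with 80% certainty".
- Criterion to which this power is attached: "the lower limit of the one-sided 95% confidence interval (or equivalently a 90% two-sided confidence interval) will be above the non-inferiority limit of 7" per cent.

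The Study objectives section frames the aim as safe introduction with no rise in 90-day complications. The Statistical analysis section gives chi-square tests and a 0.05 significance level, and does not restate the non-inferiority rule. The decisions it leaves to the later analysis plan are stratification, subgroups and baseline imbalance.

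**The concern.** A higher value of this endpoint is worse, and the margin is the largest increase that will be tolerated. Non-inferiority then means that the upper limit for new minus control lies below +7 points or, equivalently, that the lower limit for control minus new lies above −7 points. The last sentence of the section mixes the two forms: it takes the lower limit, sets it above the margin, and has no minus sign. It does not say which rate is subtracted from which.

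The rule as worded therefore describes a different finding from the one the study is designed to make, and the 80% attached to it does not belong to it. If the sentence is put right only after results are known, the limit, the sign and the contrast could all appear to have been chosen in hindsight.

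**Working it through.** **Inputs (Sample size calculation section).** Control rate 0.26; margin 0.07; one-sided 5%, from "one-sided 95% confidence interval (or equivalently a 90% two-sided confidence interval"; power 80%; 365 per cohort. The rate under the new technique is taken as 0.26, inferred from the no-difference assumption. The allocation is not stated, so two contrasts are tried: control against both intervention cohorts pooled (365 vs 730), and control against one cohort (365 vs 365). The normal approximation with unpooled variance is used throughout. The variance term is 0.26 × 0.74 = 0.1924.

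**Step 1: reproduce the planned size.** Using the conventional rule, with r the ratio of intervention to control patients:

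n(control) = (1.645 + 0.842)² × 0.1924 × (1 + 1/r) / 0.07²

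- r = 2: 364.1, rounded up to 365 controls and 1095 in total, which matches the article.
- r = 1: 486 per cohort, no match.
- At one-sided 2.5%: 463 controls (r = 2) or 617 (r = 1), no match.

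The stated size thus follows from the conventional rule with the two intervention cohorts pooled.

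**Step 2: what the worded rule requires.** SE = √[0.1924 × (1/n₁ + 1/n₂)] and half-width = 1.645 × SE. The worded rule needs an observed difference above 0.07 + half-width. The conventional rule allows an observed increase of up to 0.07 − half-width.

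**Step 3: probability of meeting each rule when both true rates are 26%.** Worded rule: 1 − Φ(0.07/SE + 1.645). Conventional rule: Φ(0.07/SE − 1.645).

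| Quantity | 365 vs 730 | 365 vs 365 |
|---|---|---|
| SE | 0.0281 | 0.0325 |
| Half-width, points | 4.6 | 5.3 |
| Worded rule: observed difference needed, points | 11.6 | 12.3 |
| Worded rule: probability | 0.002% | 0.007% |
| Conventional rule: largest observed increase allowed, points | 2.4 | 1.7 |
| Conventional rule: probability | 80.1% | 69.5% |

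If the variance is taken at the observed rates instead of at 26% in both groups, the difference needed under the worded rule is about 11.8 points (harm) or 11.4 points (benefit) for 365 vs 730. For 365 vs 365 it is about 12.7 or 11.8 points.

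**Step 4: the two readings of the worded rule.**

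- New minus control: it is met only by demonstrated harm beyond the margin, which the 33% ceiling rules out as safe. For an 80% chance of meeting it with 365 vs 730, the true rate under the new technique would have to be about 40.3%.
- Control minus new: it is met only by a demonstrated reduction of more than 7 points. For an 80% chance, the true rate would have to be about 12.5%.

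Reading the interval as one for the complication rate itself does not help. At a rate of 26%, a lower limit above 7% would be met trivially.

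**The case against.** The strongest reply is that the intended meaning is recoverable. The 33% ceiling, in the same section, gives the direction of tolerated harm correctly. The objectives agree with it, and the planned size is reproduced only in the conventional direction. A lower limit above the margin is also the usual phrasing for control minus new against −7%, so the slip may be no more than a missing minus sign. The sentence describes power and is not set out as an analysis rule.

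Most of this stands, and it limits the point. A reader might infer that the study was powered in the wrong direction, that it cannot succeed when the techniques are equally safe, or that it would declare a harmful technique safe. The documents support none of these: each requires the sentence to be applied while the ceiling, the objective and the sample size are ignored. Nor can it be said that the article gives no correct statement of what counts as safe, because the ceiling is one.

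What the reply does not remove is that the ceiling is expressed as a rate and says nothing about a confidence limit. The only sentence that does so is wrong as worded. A statistical analysis plan may state the rule correctly, but that would not make this sentence right.

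**Conclusion.** The point holds as an internal contradiction in wording: the confidence-limit form of the criterion has the wrong limit or the wrong sign, and disagrees with the 33% ceiling and the objective. The very small probabilities measure how far the wording departs from the intended rule. They do not forecast a wrong trial conclusion.

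The figures assume true rates of 26% in both groups and the normal approximation. The 0.002% and 80.1% also assume that the implementation and consolidation cohorts are pooled against control. The article does not state this, although its sample size is reproduced only in that way. With a single cohort against control, the figures are 0.007% and 69.5%. The conclusion about the wording is the same under either contrast. The size of the study is not affected by the correction.

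**What to change.** Replace the last sentence of the Sample size calculation section with a rule on these lines:

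> Non-inferiority is concluded if the upper limit of the two-sided 90% confidence interval (one-sided 95%) for the risk difference in 90-day complications, standardised technique minus control, is below +7 percentage points.

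In the same place, name the contrast to which the 80% applies. With 365 per cohort, 80% is reproduced only when the implementation and consolidation cohorts are pooled against control. If a single cohort against control is meant, the power to quote is about 70%. The analysis plan should carry the same wording, fixed before the data are locked.

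The cost is one sentence and a named contrast. The correction itself needs no new patients, data or recalculation of the sample size.
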